### 2.2. Inclusion and Exclusion Criteria

For a full overview of all inclusion and exclusion criteria, see Table 1.

### 2.3. PBM Protocols

#### 2.3.1. Transcutaneous PBM

Patients will receive transcutaneous PBM using the ATP38^®^ device (Swiss Bio Inov S.A., Moudon, Switzerland). They will be either seated or lying down during the procedure. Three light-emitting panels will be positioned around the patient’s oral cavity—one in front of the lips and two on each side of the cheeks—by a State Registered Nurse or a Medical Electroradiology Technician. Protective glasses will be provided for the duration of the session. The device will emit infrared light ranging from 600 to 820 nm, a wavelength range selected for its ability to effectively penetrate soft tissues while minimizing absorption by superficial structures, thereby allowing deeper energy delivery to the oral mucosa [35]. The power density of 2 J/cm^2^ for preventive treatment and 6 J/cm^2^ for curative treatment aligns with previous studies demonstrating optimal tissue stimulation and anti-inflammatory effects within this fluence range while avoiding potential photoinhibition effects at higher doses [21].

The average irradiation duration of 240 s for preventive therapy and 720 s for curative therapy will ensure that the total energy delivered per session remains within the recommended range for effective PBM while maintaining a practical treatment duration for clinical application [33]. Sessions will be administered twice weekly as a preventive measure and three times weekly if OM ≥ grade 1 develops, following prior clinical trials that demonstrated a significant reduction in mucositis severity with a similar treatment frequency [36].

#### 2.3.2. Intraoral PBM

Patients will receive intraoral PBM using the CareMin650™ device (NeoMedLight, Villeurbanne, France), with two intraoral pads (CareMin650™ Oral Pad) positioned within the oral cavity while seated. The device will emit red light at 650 nm, a wavelength chosen for its superior absorption by epithelial and subepithelial tissues, maximizing local bio-stimulation [21]. The power density of 3 J/cm^2^ for preventive treatment and 6 J/cm^2^ for curative treatment is based on evidence indicating that this fluence range effectively promotes wound healing and reduces inflammation while remaining within the safety threshold for oral tissues [35]. The average irradiation duration of 138 s for preventive therapy and 260 s for curative therapy was selected to ensure an appropriate energy dose while minimizing patient discomfort [33]. The procedure will be performed by a State Registered Nurse or a Medical Electroradiology Technician, ensuring strict adherence to the pain-free application rule when placing the oral pads. The treatment schedule will follow the same protocol as that of transcutaneous PBM.

### 2.4. Standard Supportive Care Measures

All patients enrolled in this study will receive standard preventive and therapeutic care for OM, in accordance with established national and international oncology guidelines. Preventive strategies will include systematic oral hygiene protocols, routine dental evaluations, the use of bicarbonate-based mouth rinses, and recommendations for adequate hydration. These measures will be implemented uniformly across both treatment groups. In the event of OM development, patients will be managed according to clinical needs using standard interventions such as topical analgesics, mucosal protectants, and systemic analgesia, following institutional supportive care protocols.

The use of any concomitant treatments—including pharmacological agents (e.g., antifungals, corticosteroid-based rinses, local anesthetics), dietary modifications, or additional supportive measures—will be systematically recorded for each patient throughout the study. This approach will ensure both ethical patient care and the ability to account for potential confounding factors when evaluating the effects of intraoral versus transcutaneous PBM.

### 2.5. Data Collection

Data will be collected from electronic medical records and will include demographics, clinical history, treatment details, and outcomes. Weekly evaluations of OM will be performed by clinicians independent from PBM administration and unaware of group allocation using National Cancer Institute Common Terminology Criteria for Adverse Events (NCI-CTCAE) v5.0 criteria. Additional data will include visual analog scale pain scores, the quality of life questionnaires European Organisation for Research and Treatment of Cancer Quality of Life Questionnaire–Core 30 (EORTC QLQ-C30) and European Organisation for Research and Treatment of Cancer Quality of Life Questionnaire–Head and Neck Module (EORTC QLQ-HN35) [37,38], and nutritional intake using the Simple Evaluation of Food Intake (SEFI) tool.

### 2.6. Statistical Analysis

Descriptive statistics will summarize the patient demographics and clinical characteristics. Quantitative variables will be expressed as mean ± standard deviation, while categorical variables will be presented as frequencies and percentages. Between-group comparisons will be conducted using appropriate statistical tests, including t-tests for continuous data and chi-squared tests for categorical data. A significance level of *p* < 0.05 will be considered statistically significant.

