### 1.1. Oral Mucositis: A Major Clinical Challenge

OM is an acute inflammatory condition that affects 59–100% of patients receiving radiotherapy for oral cavity and oropharyngeal cancers, leading to painful ulcerative lesions that impair swallowing, nutrition, and overall quality of life [7,8]. Severe cases can result in treatment delays or dose reductions, which may compromise oncological outcomes [9,10,11,12]. Current treatment options, such as topical agents (e.g., medicated mouthwashes) and systemic analgesics, provide suboptimal relief, highlighting the urgent need for more effective strategies [13,14].

Several alternative or adjunctive strategies have been investigated for the management of OM in cancer patients. Histatin-5 mucoadhesive gel, a salivary antimicrobial peptide formulation, has shown promising results in preclinical and in vivo studies for promoting mucosal healing [15]. Bioadhesive agents, which form protective films over ulcerated mucosa, have also demonstrated efficacy in reducing mucositis severity and improving patient comfort, as confirmed by a recent systematic review and meta-analysis [16]. Furthermore, herbal medicine is being explored as a supportive care option to alleviate radiation-induced mucosal toxicity, particularly in traditional Asian medicine contexts [17]. At the molecular level, the keratinocyte growth factor (KGF)/KGF receptor (KGFR) pathway has been identified as a dual therapeutic target for both epithelial repair and cancer regulation, offering potential in mucosal protection strategies during cancer treatment [18].

These approaches complement light-based therapies, which remain among the most extensively studied interventions for mucositis prevention and treatment in oncology [10].

Radiation-induced OM is a multi-phase pathological process triggered by direct cytotoxic damage to epithelial cells, leading to inflammatory cascades, reactive oxygen species generation, and further tissue breakdown. Predictive modeling has identified key risk factors for severe OM, including treatment acceleration, mean radiation dose to the oral cavity, smoking status, and patient gender [19,20].

Given the complexity of OM pathogenesis and its profound impact on patient outcomes, novel therapeutic approaches are warranted.

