## 2. Materials and Methods

### 2.1. Study Setting

This randomized pilot study will be conducted at the Institut de Cancérologie Strasbourg Europe (ICANS), France, in the University Department of Radiotherapy and the Department of Oncology Supportive Care. The study will aim to compare the efficacy of transcutaneous and intraoral PBM in preventing and managing OM in patients receiving radiotherapy for cancers of the oral cavity and oropharynx. The study will follow a randomized 1:1 allocation of patients to either the transcutaneous PBM or intraoral PBM group, with stratification based on tumor location, prior surgery, and chemotherapy regimen.

This study was registered on clinicaltrials.gov in November 2024 (NCT06458517).

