### 2.8. Objectives

#### 2.8.1. Primary Endpoint

The primary outcome measure of this study is the reduction in the incidence of OM (grade ≥ 2) in patients undergoing radiotherapy or chemoradiotherapy for cancers of the oral cavity or oropharynx. The comparison will be based on the method of PBM delivery: transcutaneous versus intraoral.

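### The randomisation is stratified by three factors, but the only tests named in section 2.6 do not use them. If the factors are prognostic, the comparison is conservative and loses some power.

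*Protocol article*

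**What the plan says.** Section 2.1 (Study Setting) fixes a 1:1 randomisation between the two delivery methods, "with stratification based on tumor location, prior surgery, and chemotherapy regimen". It does not give the number of levels of each factor or the allocation method.

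Section 2.6 (Statistical Analysis) names the analysis: "Between-group comparisons will be conducted using appropriate statistical tests, including t-tests for continuous data and chi-squared tests for categorical data", at the 0.05 level. It mentions no stratified test, regression model or covariate, and neither does any other section. Section 2.4 says that concomitant treatments are recorded so that confounding can be taken into account, but it gives no method and does not refer to the stratification factors.

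Section 2.8.1 defines the primary outcome through the incidence of grade 2 or higher OM, a yes/no outcome per patient. Of the two tests named, the chi-squared test is the one that applies. For the continuous outcomes, section 2.5 says: "Additional data will include visual analog scale pain scores, the quality of life questionnaires". The t-test is the one named for data of that kind.

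**The concern.** Stratified randomisation makes the arms alike on the stratification factors. Outcome differences between strata then no longer add to the chance variation of the treatment comparison. A plain chi-squared test still counts those differences as noise. Its standard error is then too large, its true error rate falls below the nominal 5%, and it has less power than an analysis that uses the factors.

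At stake is precision. The Discussion (section 3) itself lists the small sample as a limitation, so the trial has little information to spare. The benefit bought at randomisation is partly given away at the analysis.

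**Working it through.** The article states no sample size, power, effect size or grade 2 or higher rate, so there is no figure to reproduce. The size of the effect has to be explored under assumptions.

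**Inputs from the article:** 1:1 allocation and three stratification factors (section 2.1); chi-squared test at 0.05 (section 2.6, taken as two-sided); binary primary endpoint (section 2.8.1).

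**Assumed inputs:** two levels per factor, so 2 × 2 × 2 = 8 strata of equal expected size; permuted blocks of 4 within strata; N = 40, 80 or 160; control rate 50% or 70%; the same odds ratio (OR) of 1, 2, 3 or 5 for each factor; treatment OR 0.3 (N = 40, 80) or 0.4 (N = 160). For OM, the Introduction (section 1.1) says only that it "affects 59–100% of patients receiving radiotherapy for oral cavity and oropharyngeal cancers", with no grade attached, so it does not supply the rate needed.

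**Step 1: large-sample formula.** Let p_s be the event rate in stratum s under no treatment effect and p the overall rate. The plain test uses a variance proportional to p(1 − p). With balance inside strata, the true variance is proportional to the mean of p_s(1 − p_s), which equals p(1 − p) − Var(p_s). The ratio is R = 1 − Var(p_s) / [p(1 − p)], and the true two-sided error is 2 × [1 − Φ(1.96 / √R)].

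At p = 0.5, the four distinct stratum logits are ±1.5 ln(OR) and ±0.5 ln(OR), with weights 1/8, 3/8, 3/8 and 1/8.

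- OR 2: rates 0.261, 0.414, 0.586, 0.739. Var = 0.25 × 0.2388² + 0.75 × 0.0858² = 0.0198. R = 1 − 0.0198/0.25 = 0.921. 1.96/√0.921 = 2.042. Error = 4.1%.
- OR 3: rates 0.161, 0.366, 0.634, 0.839. Var = 0.25 × 0.3386² + 0.75 × 0.1340² = 0.0421. R = 1 − 0.0421/0.25 = 0.831. 1.96/√0.831 = 2.149. Error = 3.2%.

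**Step 2: simulation.** This compares the uncorrected chi-squared test with the Cochran-Mantel-Haenszel (CMH) test on the 8 cells. There were 100,000 null and 50,000 alternative replicates per setting, giving simulation errors of about √(0.05 × 0.95/100,000) = 0.07 points for the error rate and at most √(0.25/50,000) = 0.22 points for power. Ranges run over the three values of N and the two control rates.

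| OR per factor | True error, chi-squared | Power, CMH minus chi-squared (points) |
|---|---|---|
| 1 | 4.6–5.7% | −2.6 to +0.1 |
| 2 | 4.0–4.7% | +0.2 to +2.6 |
| 3 | 3.2–3.9% | +3.9 to +6.5 |
| 5 | 2.1–2.9% | +8.0 to +13.4 |

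CMH holds 4.8% to 5.0% throughout. The spread around 5% for the chi-squared test at OR 1 comes from the discreteness of small tables. At N = 160 and a control rate of 50%, the simulated errors of 4.0% (OR 2) and 3.2% (OR 3) agree with step 1.

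Examples at a control rate of 70%, power of chi-squared against CMH:

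| N | OR 1 | OR 2 | OR 3 |
|---|---|---|---|
| 40 | 44.3% / 43.2% | 39.0% / 40.5% | 31.8% / 36.4% |
| 80 | 76.4% / 74.2% | 70.3% / 70.8% | 61.4% / 65.9% |

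The t-test part was not simulated. The same variance argument applies to it.

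**The case against.** Four points can be made in defence of the plan.

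- **The list is open and the article is condensed.** Section 2.6 speaks of appropriate tests and introduces the two it names with the word *including*. A full protocol or analysis plan may specify adjustment. This stands, so it cannot be said that the trial will analyse its primary endpoint without adjustment. What can be said is that the only tests the article names do not use its design. If another document adjusts, section 2.6 needs the same correction so that the two agree.
- **The factors may not be strong predictors.** A reader might take them to be established strong risk factors for OM. The article does not say so. The key risk factors for severe OM in section 1.1 are others, "including treatment acceleration, mean radiation dose to the oral cavity, smoking status, and patient gender", and none of these is a stratification factor. This stands. Choosing the three for stratification presumes that they matter, but their strength is unknown, and the size of the effect depends on it.
- **The test remains valid.** A reader might infer from an error rate different from 5% that false positives are inflated. The opposite holds: ignoring the strata pushes the error below 5%. The point concerns efficiency only.
- **Stratifying can cost power.** With 8 cells, 40 patients average 40/8 = 5 per cell. If the factors carry no information, CMH loses up to 2.6 points at N = 40 to 80. This stands and belongs in the decision.

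On pain and quality of life, the visible text does not say when these are measured, and the trial schema is not shown. Baseline adjustment can therefore be recommended only where a baseline score exists.

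**Conclusion.** The point holds as a mismatch between design and named analysis. It is a worthwhile, low-cost improvement and not a threat to validity. At assumed odds ratios of 2 to 3 per factor, the plain chi-squared test has a true error of about 3% to 4.7% and loses about 0 to 7 power points. At an odds ratio of 5 per factor the loss would reach 8 to 13 points, but nothing in the article supports factors of that strength. At an odds ratio of 1 there is nothing to gain and a little to lose. All of this depends on the assumed sample size, event rates, eight equal strata, blocks of 4 and factor strength. With other allocation methods or more factor levels the figures would differ.

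**What to change.** In section 2.6, name as primary analysis of grade 2 or higher OM a comparison that accounts for tumor location, prior surgery and chemotherapy regimen. Two suitable forms are:

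- a Mantel-Haenszel risk difference with 95% confidence interval and CMH test; or
- a logistic regression with the three factors as main effects, reported as a standardised risk difference. This needs fewer terms than full cross-classification, which helps if cells are sparse. It was not simulated here.

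Fix in advance, without reference to outcomes by arm, which levels are pooled when a stratum is sparse. Keep the unadjusted chi-squared test as a sensitivity analysis.

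Where baseline pain and quality-of-life scores are collected, replace the plain t-test with ANCOVA, or a mixed model for repeated scores, containing the baseline score and the same factors.

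The cost is one paragraph of text. The stratification factors are known at randomisation, so the primary analysis needs no new data. The baseline-adjusted analyses need baseline scores, whose collection should be confirmed. The statistical price is a loss of up to about 3 power points at 40 to 80 patients if the factors prove not to be prognostic.

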### 2.7. Ethical Approval

This study will be conducted in accordance with the Declaration of Helsinki and was reviewed and approved by the Protection of persons Committee (CPP) Île-de-France, under the national registration number 2023-A02113-42 (internal reference: 2022-018, SI file number: 24.01626.000309). Authorization was also granted by the French National Agency for the Safety of Medicines and Health Products (ANSM) on 19 April 2024, under the same national IDRCB number (2023-A02113-42), as a Category 4.2 clinical investigation. The sponsor of the study is the Institut de Cancérologie Strasbourg Europe (ICANS). All participants will provide written informed consent prior to inclusion in the study.

### 2.8. Objectives

#### 2.8.1. Primary Endpoint

The primary outcome measure of this study is the reduction in the incidence of OM (grade ≥ 2) in patients undergoing radiotherapy or chemoradiotherapy for cancers of the oral cavity or oropharynx. The comparison will be based on the method of PBM delivery: transcutaneous versus intraoral.

#### 2.8.2. Secondary Endpoints

Treatment interruptions: comparison of the number and duration of treatment interruptions (radiotherapy or chemoradiotherapy), exceeding or below 7 days, between the two PBM delivery methods.Mucositis duration: comparison of the total duration of OM (all grades) between transcutaneous and intraoral PBM methods.Unplanned hospitalizations: evaluation of the number of unplanned hospitalizations during treatment in both groups.Nutritional support: comparison of the time to initiation and frequency of artificial nutrition (enteral or parenteral) between the two PBM groups.Pain and analgesic use: assessment of differences in patient-reported pain levels and analgesic consumption between the two PBM methods.Quality of life: evaluation of the impact of PBM methods on patients’ quality of life.Infection rates: comparison of local and systemic infection rates, graded by NCI-CTCAE v5.0, between the two groups.Xerostomia: evaluation of xerostomia incidence and severity (all grades) in patients treated with each PBM method.

### 2.9. Participant Timeline

Figure 1 shows the different stages of the clinical trial.

### 2.10. Project Duration and Expected Outcomes

#### 2.10.1. Project Duration

The study is expected to span a total duration of 20 months, including an 18-month recruitment period and a 2-month follow-up phase for each participant. The investigation will begin on 1 February 2025, and conclude on 1 October 2026. This timeline will allow sufficient time for patient enrollment, data collection, and initial analysis.

#### 2.10.2. Expected Outcomes

The study aims to generate robust comparative data on the efficacy of transcutaneous versus intraoral PBM in the prevention and management of OM among patients undergoing radiotherapy or chemoradiotherapy. By addressing this critical aspect of supportive care, the findings are expected to contribute significantly to the optimization of treatment outcomes and patient well-being.

One of the primary outcomes anticipated is the identification of the most effective PBM delivery method in reducing the incidence, severity, and duration of OM. This insight will not only enhance clinical understanding but also support the adoption of tailored approaches to mitigate the burden of this common complication. Additionally, the study is expected to shed light on PBM’s broader impact on patient care, particularly in terms of reducing treatment interruptions, minimizing unplanned hospitalizations, and improving pain management and quality of life.

Furthermore, the results are likely to inform the development of standardized, evidence-based protocols for PBM application in clinical settings, ensuring consistent and effective use of this therapy across diverse patient populations. Lastly, the study will provide foundational data for future research, serving as a basis for larger multicenter trials and long-term evaluations of PBM’s efficacy and safety.

Ultimately, these findings are expected to bridge current gaps in clinical practice, paving the way for improved supportive care strategies for patients undergoing radiotherapy for head and neck cancers. By achieving these outcomes, the study will contribute to both advancing scientific knowledge and enhancing patient outcomes in this challenging treatment context.

## 3. Discussion

OM is a frequent and debilitating side effect of radiotherapy and chemoradiotherapy in patients with head and neck cancer, leading to significant impairments in nutritional intake, treatment continuity, and overall quality of life. Despite advancements in supportive care, existing preventive measures remain limited in efficacy [14].

PBM therapy has gained increasing recognition as an effective non-pharmacological intervention for OM. Its mechanisms—including reduction in inflammation, promotion of epithelial healing, and analgesic effects—have been well documented [21,22]. In 2019, MASCC/ISOO published guidelines recognizing PBM as a recommended intervention for the prevention of OM in various cancer populations [10,21].

Several randomized controlled trials have confirmed PBM’s efficacy [39,40,41,42,43,44]. Gouvêa De Lima et al. demonstrated that intraoral low-level laser therapy significantly reduced the incidence and severity of OM in head and neck cancer patients receiving concurrent chemoradiotherapy [45]. A recent meta-analysis with a trial sequential analysis confirmed the efficacy of PBM in reducing the severity and duration of chemotherapy-induced OM, providing conclusive evidence with moderate certainty. Khalil et al. further reported that PBM preconditioning not only decreased OM incidence but also improved quality of life in adult chemotherapy patients [26]. These results collectively support PBM’s clinical relevance in oncology supportive care.

However, while intraoral PBM has shown robust efficacy, its tolerability and logistical constraints (e.g., need for direct contact, patient discomfort) have prompted interest in alternative approaches such as transcutaneous PBM. A randomized controlled trial compared intraoral versus extraoral PBM in hematopoietic stem cell transplant recipients, reporting similar effectiveness in OM prevention, though intraoral PBM provided more localized therapeutic effects [33].

Additionally, Zecha et al. highlighted the need for well-defined safety parameters in PBM application through their systematic review on laser therapy, underscoring the importance of optimizing wavelength, dose, and delivery technique [10,21].

The present study addresses this clinical gap by directly comparing intraoral and transcutaneous PBM delivery methods using standardized protocols in head and neck cancer patients receiving (chemo)radiotherapy. The study’s strengths include its prospective randomized design, the use of clearly defined PBM parameters for both modalities, and a comprehensive evaluation of outcomes including OM incidence, pain levels, treatment interruptions, nutritional support, and quality of life. However, limitations include its single-center design and relatively small sample size, typical of pilot studies. Additionally, the lack of a third arm without PBM limits the interpretation of absolute efficacy. Nevertheless, the comparative design offers critical insights into the relative benefits and feasibility of each PBM modality in a real-world clinical setting.

Future studies should expand upon these findings by incorporating larger, multicenter cohorts and extended follow-up periods. Such follow-up is essential not only to confirm sustained benefits but also to monitor for potential long-term adverse effects of PBM, such as the risk of secondary malignancies in the oral cavity. Bezinelli et al. conducted a 15-year retrospective study investigating different PBM protocols for OM control in hematopoietic cell transplantation patients [46]. They found no immediate adverse effects or secondary malignancies associated with PBM, suggesting the long-term safety of the therapy. However, further research with extended follow-up is necessary to corroborate these findings and ensure the comprehensive safety profile of PBM in oncology supportive care.

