### 1.3. Justification for the Comparison Between Intraoral and Transcutaneous PBM

PBM relies on the application of low-intensity light to stimulate biological processes, particularly the reduction in inflammation and the acceleration of tissue repair. The effectiveness of this approach is influenced by several parameters, including wavelength, applied dose, and the depth of light penetration in biological tissues. Studies on light penetration in both intraoral and extraoral tissues have demonstrated that wavelengths in the red spectrum (600–700 nm) and near-infrared spectrum (700–1000 nm) exhibit different penetration capacities depending on the medium they traverse. Intraoral PBM, applied directly to the oral mucosa, allows for the efficient transmission of photon energy to the epithelial and subepithelial layers, thereby maximizing local bio-stimulation [21]. Additionally, studies have shown that the extraoral application of near-infrared phototherapy can significantly reduce mucositis-related pain in patients undergoing hematopoietic stem cell transplantation, suggesting that transcutaneous PBM may be effective despite potential energy loss due to tissue absorption [30].

A study by Jagdeo et al. evaluated light diffusion through various thicknesses of human tissues and demonstrated that photon intensity decreased exponentially with depth, particularly in highly vascularized and dense tissues [31]. This suggests that intraoral PBM may have a significant advantage in directly targeting mucosal lesions, whereas transcutaneous PBM may be more suitable for deeper or less accessible areas (Huang et al., 2009) [32]. Bensadoun et al. highlighted that while both intraoral and extraoral PBM approaches were effective for managing OM, intraoral PBM ensured the direct irradiation of mucosal tissues, optimizing energy absorption and therapeutic efficacy [22]. In contrast, extraoral PBM, particularly with near-infrared wavelengths, may reach intraoral structures indirectly but is subject to potential energy loss due to absorption and scattering by intermediate tissues.

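### Route of delivery is fully confounded with device, wavelength, preventive fluence and session time, so the trial supports a conclusion about two device regimens, not about route alone

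*Protocol article*

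**What the plan says.** Section 2.8.1 (Primary Endpoint) compares the incidence of grade 2 or higher oral mucositis (OM) between the arms and defines the contrast by how PBM is delivered, transcutaneous against intraoral. Section 2.10.2 (Expected Outcomes) anticipates "identification of the most effective PBM delivery method in reducing the incidence, severity, and duration of OM". Section 4 (Conclusions) asks whether intraoral PBM does better and characterises it by its targeting of the affected tissue. Section 3 (Discussion) presents the study as "directly comparing intraoral and transcutaneous PBM delivery methods using standardized protocols".

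Sections 2.3.1 and 2.3.2 define the arms. In one, "Patients will receive transcutaneous PBM using the ATP38^®^ device", and "The device will emit infrared light ranging from 600 to 820 nm". In the other, "Patients will receive intraoral PBM using the CareMin650™ device", and "The device will emit red light at 650 nm". Each section also sets its own fluence and average session time; for the transcutaneous arm the fluence is given as "The power density of 2 J/cm^2^ for preventive treatment and 6 J/cm^2^ for curative treatment". Session frequency is common to both arms.

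The limitations in sections 3 and 4 are the single centre, the small sample and (section 3 only) the absence of an arm without PBM. Neither section says that the light parameters differ between the arms.

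**The concern.** The question as worded is about route, but the arms differ in several respects besides route, and every one of those differences goes with the arm. Section 1.3 lists wavelength and applied dose, alongside penetration depth, as factors that influence effectiveness. On the document's own account, then, a difference in OM incidence, or the lack of one, could come from something other than route.

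This matters because the results are meant to feed into standardized PBM protocols and larger multicentre trials (Abstract; section 2.10.2). A finding reported as favouring one route would be read as applying to that route with other devices and settings. The trial has no data on that.

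**Working it through.** The document gives no figure to reproduce on this point. The check is to set the two arm definitions side by side and see what coincides with arm. Inputs come from sections 2.3.1 (transcutaneous) and 2.3.2 (intraoral). Both sections call the J/cm² values a power density; since J/cm² is energy per area, they are read here as fluence.

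| Item | Transcutaneous | Intraoral | Same? |
|---|---|---|---|
| Device | ATP38, external panels | CareMin650, intraoral pads | No |
| Wavelength | 600–820 nm | 650 nm | No |
| Preventive fluence (nominal) | 2 J/cm² | 3 J/cm² | No |
| Curative fluence (nominal) | 6 J/cm² | 6 J/cm² | Yes |
| Preventive session time (average) | 240 s | 138 s | No |
| Curative session time (average) | 720 s | 260 s | No |
| Sessions per week, preventive / curative | 2 / 3 | 2 / 3 | Yes |

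**Nominal differences**

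- Preventive fluence ratio, intraoral to transcutaneous: 3 / 2 = 1.5.
- Weekly preventive fluence = fluence × sessions: 2 × 2 = 4 J/cm² versus 3 × 2 = 6 J/cm².
- Weekly curative fluence: 6 × 3 = 18 J/cm² in both arms.
- Session time ratio, transcutaneous to intraoral: 240 / 138 = 1.74 preventive; 720 / 260 = 2.77 curative.

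**Can the factors be separated?** There are two arms and one value of each factor per arm. Route, device, wavelength, preventive fluence and session time therefore all have the same indicator variable, namely arm. No model fitted to such data can give them separate effects.

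**Does the preventive difference bear on the primary endpoint?** Yes. Patients receive preventive sessions until OM reaches grade 1 (section 2.3.1), and the endpoint is grade 2 or higher (section 2.8.1). The phase in which nominal fluence differs thus precedes the endpoint, and equal curative fluence does not remove the issue.

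**Does the document explain the differences by route?** For wavelength, partly: section 2.3.1 justifies its range by tissue penetration and section 2.3.2 justifies 650 nm by absorption in epithelial and subepithelial tissue. For preventive fluence, no: each section cites literature for its own value, but neither gives a reason tied to route for the two values to differ.

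**The case against.** The strongest reply is that this is a pragmatic comparison and is openly presented as one. The Abstract names the device in each arm, sections 2.3.1 and 2.3.2 print the parameters, and section 3 speaks of each modality in a real-world setting. The phrase "directly comparing intraoral and transcutaneous PBM delivery methods using standardized protocols" is not false: each arm does follow a fixed protocol, and matched parameters are not claimed. Wavelength is chosen to suit the route, so a fair reading of delivery method may include it. Section 4 also leaves treatment parameters and dosimetry to later work, so the pilot is not offered as the last word.

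Most of this stands. The phrase in section 3 is not an error, disclosure of the parameters is adequate, and part of the wavelength difference belongs to the route. What it does not answer is the step from those arms to the most effective delivery method in section 2.10.2, or the missing limitation. Disclosing the settings does not narrow the conclusion drawn, and the preventive fluence difference has no stated link to route. A general call for dosimetry research does not tell the reader that this trial's own contrast is confounded.

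Two stronger readings are tempting, and neither is supported:

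- **That the intraoral arm receives 1.5 times the dose, or a multiple of the irradiance.** The document states no irradiance and does not say at which surface fluence is defined. Dividing fluence by average time gives 2 / 240 s = 8.3 mW/cm² versus 3 / 138 s = 21.7 mW/cm² in the preventive phase, and 6 / 720 s = 8.3 versus 6 / 260 s = 23.1 mW/cm² in the curative phase. These values assume that the stated average time delivers the stated fluence. Section 1.3 reports that "photon intensity decreased exponentially with depth", so a nominal figure for light applied through skin and one for light applied at the mucosa cannot be read as a ratio of dose reaching the mucosa.
- **That fluence differs throughout.** It does not: nominal curative fluence is equal.

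**Conclusion.** The point holds as a limit on inference. Route coincides completely with device, wavelength, nominal preventive fluence (2 versus 3 J/cm²) and session time (240 versus 138 s; 720 versus 260 s), so a statement about route alone does not follow from this design, whatever the result. This rests only on the parameters in sections 2.3.1 and 2.3.2 and on section 1.3's statement that wavelength and dose influence effectiveness. It does not depend on the derived irradiances.

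A reader might infer that the trial is biased or that its comparison is invalid. The documents do not support that: randomization gives a valid comparison of the two regimens as packages. How much of any observed difference would be due to each component cannot be estimated from what is given, and no direction is claimed.

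**What to change.** - In sections 2.8.1, 2.10.2 and 4, state the contrast and the conclusions as the CareMin650 intraoral regimen versus the ATP38 transcutaneous regimen, each as delivered.
- In section 2.10.2, replace the expectation of identifying the most effective delivery method with an expectation of comparing these two regimens.
- In the limitations in sections 3 and 4, add that route cannot be separated from device, wavelength, preventive fluence and session time.

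No device, dose, schedule, endpoint or analysis changes, and none is proposed. The work is a few sentences of rewording. The price is a narrower conclusion: the trial can say which regimen did better, but not that one route is better in general.
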